#### **4. Population**

##### **4.1. Inclusion criteria**

Those who meet all the following requirements:

- Age  $\geq 18$  years old and  $\leq 80$  years old, regardless of gender;
- After the onset of the disease, the National Institutes of Stroke Scale score:  $6 \leq \text{NIHSS} \leq 20$ , and the sum of the fifth upper limb score and the sixth lower limb score was  $\geq 2$ ;
- The onset time is within 48 hours (including 48 hours);
- Patients diagnosed as ischemic stroke according to "key points for diagnosis of all kinds of major cerebrovascular diseases in China 2019", with good prognosis after the first attack or the last attack (MRS score  $\leq 1$  before this attack);
- The informed consent approved by the ethics committee was voluntarily signed by the patient or his legal representative.

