**6.1. Screening period (visit 1)**

- Informed consent form
- Demographics, including age, gender, height and weight (Height and weight information of subjects with unfavorable limbs can be obtained through interrogation);
- Disease attributes;
- Past medical history and medication, disease history and medication history before enrollment;
- Vital signs and physical examination, including heart rate, blood pressure, body temperature and respiratory rate. Physical examination is evaluated by organ and system;
- Blood routine, blood biochemistry (hepatic and renal function, blood glucose (non-fasting), blood lipids, myocardial enzyme, electrolytes and homocysteine), urine routine, coagulation function and ECG examination;
- Pregnancy test (for women of childbearing age only);
- NIHSS score; (If thrombolysis subjects have completed the NIHSS for screening period before thrombolysis, the pre-thrombolysis score should be used as the basis for enrollment)
- mRS score before this onset;
- Cranial CT (plain scan);
- Cranial MRI (optional and completed during the study);
- Randomization.

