## 8. Statistical analysis

### 8.1. Determination of sample size

The objective of this study is to evaluate the efficacy and safety of Y-2 Sublingual Tablets in the treatment of acute ischemic stroke. The primary efficacy index is the proportion of subjects with mRS score  $\leq 1$  on Day 90 of treatment. The sample size is calculated based on the primary efficacy index. According to the previous clinical studies, it is expected that the proportion of subjects with mRS score  $\leq 1$  on Day 90 of treatment is 50% in the test group and 40% in the control group. Taking bilateral  $\alpha$  as 0.05, the power as 80% and the random ratio as 1:1, the sample size for each group is calculated to be 388. Considering the 15% dropout rate, then it is planned to enroll 457 cases in each group, with a total sample size of 914 cases.

An interim analysis is scheduled to be performed after approximately 50% of subjects complete the visit on Day 90. The purpose of interim analysis is to reestimate the sample size based on primary efficacy indexes. It is conducted by the Independent Data Monitoring Committee (IDMC) and whether the sample size should be increased or remain unchanged is recommended according to the regulations of the IDMC. The sample size may be increased to 1.5 times the scheduled sample size at most, and won't be reduced.

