Unblinding sample size will be re-estimated in the interim analysis. If sample size adjustment occurs, the CHW method will be used to weight the test statistics in the final analysis, and the *P* value of the hypothesis testing will be estimated accordingly for statistical inference.

Similar approaches were used for binary secondary outcomes, including mRS score  $\leq 2$  on day 90, NIHSS score  $\leq 1$  on day 14, 30, and 90, and safety outcomes on adverse events and treatment related adverse events. For mRS score on day 90, an ordinal logistic regression analysis was performed, with the results presented as common OR and 95% CI, where a common OR in favor of Y-2 sublingual tablet was  $>1.0$ . For changes in NIHSS score from baseline to day 14, means with 95% CIs were calculated for each group, and the mean differences with 95% CI between the groups were estimated by generalized linear regression.

In addition, a post hoc sensitivity analysis was performed using different approaches to impute missing data on the primary efficacy outcome. Finally, the treatment effects on the primary outcome were analyzed among several prespecified subgroups by including the interaction between treatment and subgroup effect into the logistic regression model.

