#### **4.1.1 Significant Level**

Unless otherwise specified, all efficacy analyses will be statistically tested at a 2-sided significance level  $\alpha = 0.05$  to calculate nominal p values, point estimates of efficacy differences, and 2-sided 95% confidence intervals.

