  - Concomitant medication end date is only missing for Day: Impute as last day of month.
  - Date of first dose appointment: Date of start of treatment period

Dates in the data listings were listed as completed on the eCRF.

- 3) Definition of baseline: The last non-missing data before the first dose is baseline. If a subject took trial medication but did not have a date of first dose, the last non-missing data prior to the date of enrollment was taken as baseline.
- 4) Change from baseline was defined as: test value at post-treatment follow-up – baseline test value.

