Missing data on the primary efficacy outcome was imputed with LOCF combined with best case analysis (assume any subject missing 90-day outcome after LOCF to be mRS score  $\leq 1$ ). Logistic regression analysis was performed to calculate the OR and 95% confidence interval.

Sensitivity Analysis 4:

Missing data on the primary efficacy outcome was imputed with LOCF combined with worst case analysis (assume any subject missing 90-day outcome after LOCF to be mRS score  $> 1$ ). Logistic regression analysis was performed to calculate the OR and 95% confidence interval.

Sensitivity Analysis 5:

Logistic regression analysis was performed to calculate the OR and 95% confidence interval between the investigational and control groups using treatment as the analysis variable and baseline time from actual treatment to onset ( $\leq 24$  hours,  $> 24$  hours), and study site as covariates.

- Subgroup analysis

The primary efficacy endpoint will be analyzed in subgroups according to the following factors:

- Age ( $\leq 65$ ,  $> 65$ )
- Gender (male, female)
- Actual treatment to Onset Category 1 ( $\leq 24$  hours,  $> 24$  hours)

- 
- Premorbid mRS score (0, 1)
  - Pre-treatment NIHSS total score classification ( $\leq 7$ ,  $> 7$ )
  - History of stroke (Yes, No)
  - History of hypertension (Yes, No)
  - History of hyperlipidemia (Yes, No)
  - History of diabetes (Yes, No)
  - History of heart disease (yes, no)
  - Stroke etiology classification
  - Renal function class (normal, mild impairment and moderate to severe impairment as assessed by baseline eGFR)

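### Effect modification by stroke severity is tested only as NIHSS ≤7 versus >7; a treatment × continuous NIHSS term would use the recorded score better, as a cheap exploratory addition

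*Combined protocol and SAP*

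**What the plan says.** - **Entry range.** Protocol 4.1, in the criterion that begins "After the onset of the disease, the National Institutes of Stroke Scale score", admits scores from 6 to 20 inclusive.
- **Severity subgroup.** SAP 4.3.1 lists "Pre-treatment NIHSS total score classification" with two classes, ≤7 and >7. No reason is given for the cut at 7.
- **Test.** Protocol 8.4 examines subgroups "by including the interaction between treatment and subgroup effect into the logistic regression model". SAP 4.3.1 lists the factors but names no interaction test.
- **Elsewhere.** NIHSS is not a randomisation stratum (Protocol 5.3, SAP 2.6). It is not a covariate in Sensitivity Analysis 5, which adjusts for onset-to-treatment time and site.
- **Data.** The NIHSS total is collected at Visit 1 (Protocol 6 and 6.1). For thrombolysed patients already scored before thrombolysis, "the pre-thrombolysis score should be used as the basis for enrollment". SAP 4.1.3 defines baseline differently: "The last non-missing data before the first dose is baseline".

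The documents give no expected or observed NIHSS distribution.

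**The concern.** Of the 15 eligible scores, two (6 and 7) form one class and thirteen (8 to 20) form the other. The planned interaction therefore compares the mildest eligible strokes with all the rest, and a patient at 8 counts the same as a patient at 20. If benefit fades or grows steadily with severity, that contrast uses only part of what the recorded scores can show.

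Readers of a trial spanning NIHSS 6 to 20 will ask whether the effect holds in more severe stroke. As planned, the answer is one pooled estimate for everyone above 7. A non-significant interaction could be taken as reassurance when the test had little chance of finding a gradient.

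**Working it through.** **Inputs from the documents.** Scores 6 to 20 (Protocol 4.1); cut at 7 (SAP 4.3.1); 914 patients, all in the full analysis set; two-sided 5% level (SAP 4.1.1). The design rates are "50% in the test group and 40% in the control group" (Protocol 8.1), so the mean odds ratio is (0.50/0.50)/(0.40/0.60) = 1.5. The plan states no information or power figure for this analysis, so there is none to reproduce.

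**Assumptions.** The NIHSS distribution, the slope of the log odds ratio per point, and the prognostic effect of NIHSS.

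**Step 1: information kept for a linear trend.** This is the squared correlation between the score and the indicator for >7:

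kept = p(1 − p) × d² / V

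where p is the share above 7, d the difference between the class means, and V the variance of the score.

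- Uniform over 6 to 20: p = 13/15, d = 14 − 6.5 = 7.5, V = (15² − 1)/12 = 18.67. Kept = 0.1156 × 56.25 / 18.67 = 0.35, so 65% is lost.
- The best single cut for that shape is 12/13: p(1 − p) = (7/15)(8/15) = 0.2489, and d is again 7.5. Kept = 0.2489 × 56.25 / 18.67 = 0.75, so 25% is lost even then.

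The same formula for right-skewed (truncated geometric) shapes gives:

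| Patients scoring 6–7 | Lost with the cut at 7 |
|---|---|
| 13% (uniform) | 65% |
| 24% | 59% |
| 37% | 53% |
| 44% | 50% |
| 51% | 46% |
| 64% | 39% |
| 75% | 33% |

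Across these shapes the best single cut loses 25% to 33%. If 5% to 20% of patients have pre-treatment scores below 6, the cut at 7 loses about 40% to 51%.

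**Step 2: interaction power.** Take P(k) proportional to exp(−0.2(k − 6)), which puts 35% of patients at 6–7, with mean 9.73. A fading slope s gives OR(k) = 1.5 × exp(−s(k − 9.73)). For s = 0.08 this is 1.5 × exp(0.298) = 2.0 at NIHSS 6 and 1.5 × exp(−0.822) = 0.66 at 20.

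Each logistic model contains treatment, severity and their product. With z the expected Wald statistic of the product term, power = Φ(|z| − 1.96) + Φ(−|z| − 1.96).

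| Slope per point | Prognostic effect per point (log-odds) | Continuous: z, power | Split: z, power |
|---|---|---|---|
| 0.08 | none | 2.08, 55% | 1.41, 29% |
| 0.08 | −0.2 | 1.63, 37% | 1.25, 24% |
| 0.05 | none | 1.32, 26% | 0.89, 14% |
| 0.03 | none | 0.79, 12% | 0.54, 8% |

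Cross-check: (1.41/2.08)² = 0.46, which agrees with the 46% kept that step 1 gives for this distribution.

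**The case against.** The case against is substantial, and most of it limits the point rather than removing it.

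- **Thirteen of fifteen counts scale points, not patients.** A reader might infer that the cut sits at the edge of the population. In a trial weighted to mild stroke it could lie near the median. Because entry can rest on the pre-thrombolysis score, some pre-treatment scores may also fall below 6. This stands.
- **Half the information is not an established loss.** It is a mid-range value that depends on an undocumented distribution. Only the conditional range can be stated.
- **Part of the loss belongs to any two-group split.** At least about 25% goes with the best cut, and two-class rows are the usual subgroup display; age is also dichotomised. This stands, and it favours using the score over moving the cut.
- **Large power gaps need steep slopes.** At 0.12 per point the gap is wide (about 86% versus 52% to 55%), but the odds ratio then runs from about 2.3 at NIHSS 6 to 0.44 at 20, a reversal of effect. With shallow slopes and strong prognosis the gap nearly closes: 14% versus 13% at slope 0.05 and −0.3 log-odds per point.
- **Linearity is assumed.** If the effect changed in a step at 7, the split would lose nothing. Nothing in the documents suggests a step; keeping the row covers that case.
- **The consequences can be overdrawn.** A reader might infer that the primary conclusion, or a claim of benefit across 6 to 20, rests on this split. The documents contain no label claim and no plan to declare consistency across severity. The subgroup p values are nominal, and alpha and sample size are untouched.

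**Conclusion.** The point holds as a minor improvement, not as an error. The split at 7 is the only planned test of effect modification by severity, and it sets aside detail that the trial collects. For a linear trend the loss is about one third to two thirds (33% to 65%), conditional on the assumed NIHSS distribution.

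Under the 35% assumption, a fairly steep gradient of 0.08 per point is found with 55% rather than 29% power, or 37% rather than 24% if response also falls 0.2 log-odds per point. At slopes of 0.05 or less, power is at most 26% with the continuous score and about 14% with the split. The continuous term improves the test but would not settle whether a modest gradient exists. The analysis is exploratory throughout.

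**What to change.** 1. Keep the ≤7 / >7 row for display.
2. Add to SAP 4.3.1 a logistic model with treatment, pre-treatment NIHSS as a continuous main effect, and their interaction, plus one quadratic or spline check of linearity.
3. State that pre-treatment NIHSS means the last score before the first dose, so that thrombolysed patients are handled consistently.
4. Show the estimated treatment effect with its 95% CI at a few scores, for example 6, 10 and 15.
5. State that a non-significant interaction will not be read as evidence of a consistent effect across severity.

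The third IDMC minutes record agreement to lock the database. If the data are already unblinded, report this as a labelled supplementary analysis rather than as prespecified.

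The cost is a few sentences in the SAP and one figure, on data already collected. The downsides are a linearity assumption, which the check addresses, and one more exploratory test.

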#### 4.3.2 Secondary Efficacy Endpoints

Secondary efficacy endpoints were analyzed on the FAS and PPS without imputation of missing values.

- mRS score on Day 90 of treatment

Descriptive statistics were performed by treatment groups on mRS scores at Day 90 of treatment to calculate the number of non-missing subjects, mean, standard deviation, median, minimum, and maximum, and at the same time, the number and percentage of subjects with different mRS scores (including missing values) at Day 90 of treatment were calculated. an ordinal logistic regression analysis was performed, with the results presented as common OR and 95% CI, where a common OR in favor of Y-2 sublingual tablet was  $>1.0$

- Proportion of subjects with mRS score  $\leq 2$  at Day 90 of treatment

Descriptive statistics were performed on the number and percentage of subjects with mRS score  $\leq 2$  at Day 90 of treatment as previously described by treatment groups. Comparisons were made between treatment groups using the same logistic regression model as for the primary analysis.

- NIHSS score change from baseline at Day 14 of treatment

Observed values and changes from baseline in NIHSS score at each visit will be summarized descriptively by treatment groups and the number of non-missing subjects, mean, standard

deviation, median, minimum, and maximum will be calculated. Difference in NIHSS score from baseline to Day 14 was be calculated the means with 95% CIs were calculated for each group, and the mean differences with 95% CI between the groups were estimated by generalized linear regression.

- The proportion of NIHSS score of 0-1 at 14, 30, and 90 days of treatment;

The number and percentage of subjects with NIHSS scores of 0 to 1 at 14, 30, and 90 days of treatment will be calculated by treatment groups. Comparisons were made between treatment groups using the same logistic regression model as for the primary analysis.

- Other Efficacy Measures

Not applicable.

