## 2.5 Sample Size Determination

The sample size for this study was based on the primary efficacy measure, the proportion of subjects with mRS score  $\leq 1$  at Day 90 of treatment. According to previous clinical studies (see Protocol Reference 7-12), it is estimated that the proportion of subjects with mRS score  $\leq 1$  on Day 90 of treatment will be 50% in the investigational group and 40% in the control group, taking a two-sided  $\alpha$  of 0.05, a power of 80%, and a randomization ratio of 1:1. After calculation, 388 subjects are required in each group. Considering a 15% dropout rate, 457 subjects are planned to be randomized in each group, with a total sample size of 914.

An interim analysis is scheduled to be performed after approximately 50% of patients complete the visit on Day 90. The purpose of interim analysis is to re-estimate the sample size based on primary efficacy indexes. It is conducted by the Independent Data Monitoring Committee (IDMC) and whether the sample size should be increased or remain unchanged is recommended according to the regulations of the IDMC. The sample size may be increased to 1.5 times the scheduled sample size at most, and won't be reduced. If the sample size is adjusted, the method proposed by Cui et al. 1999 (hereinafter referred to as the CHW method) will be used to control type I errors in the final analysis.

Interim analyses and sample size re-estimation were performed by an Independent Data Monitoring Committee (IDMC) as detailed in Section 4.5 of this plan and in the IDMC charter.

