#### **4.1.2 Estimation of Missing Values**

Missing values were not imputed except for the primary efficacy measure. Missing value imputation methods for the primary efficacy measure are detailed in Text Section 4.3.1.

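### SAP 4.3.2 has no rule for death on the NIHSS or for AE withdrawal on mRS ≤2, so the NIHSS regressions compare survivors only and the two Day-90 mRS cut-points treat the same patients differently

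*Combined protocol and SAP*

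**What the plan says.** SAP 4.3.2 opens with the rule for every secondary efficacy endpoint: "Secondary efficacy endpoints were analyzed on the FAS and PPS without imputation of missing values". SAP 4.1.2 says the same in general terms: "Missing values were not imputed except for the primary efficacy measure".

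The rules for intercurrent events are written for the primary endpoint, mRS ≤1 at Day 90 (Protocol 2.3 and 8.4; SAP 2.4 and 4.3.1). Under them, having no mRS score after treatment starts, or leaving follow-up because of an AE, counts as failure. Protocol 2.3 also names death. For other early stops, the score closest to withdrawal is used. The four missing-data sensitivity analyses in SAP 4.3.1 also concern the primary endpoint only.

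On the scales themselves, Protocol Appendix 2 gives death an mRS score of 5. Appendix 3 explains how to score the NIHSS in coma but gives no value for death, and neither does any other section.

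For binary secondary endpoints, Protocol 8.4 says: "Similar approaches were used for binary secondary outcomes". SAP 4.3.2 uses the primary's logistic model for mRS ≤2 and NIHSS 0–1, and a generalized linear regression for NIHSS change to Day 14.

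**The concern.** A patient who dies cannot have an NIHSS assessment at later visits. With no assigned value and no imputation, that patient has no outcome in the regression and is left out. The comparison is then conditional on survival, a post-randomisation event that treatment may affect. An arm with more deaths would look better on NIHSS among those left, and an arm that kept severely affected patients alive would look worse. Nothing planned would reveal this, because the missing-data sensitivity analyses stop at the primary endpoint.

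There is a second, smaller inconsistency. A patient who leaves follow-up for an AE without a Day-90 score is a failure for mRS ≤1 and absent for mRS ≤2, so two cut-points of one scale at one visit are analysed on different patients. Such gaps are plausible. Protocol 5.7.1 generally ends data collection at withdrawal, and the withdrawal visit in Protocol 5.7.2 is only to be attempted.

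**Working it through.** **1. The plan's own figures.** Inputs: rates that "will be 50% in the investigational group and 40% in the control group" (SAP 2.5), and two-sided α "as 0.05, the power as 80% and the random ratio as 1:1" (Protocol 8.1).

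n per arm = [1.960·√(2×0.45×0.55) + 0.842·√(0.25+0.24)]² / 0.10² = (1.379 + 0.589)² / 0.01 ≈ 387.3, rounded up to 388. Allowing for dropout, 388/0.85 = 456.5, rounded up to 457.

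Both stated figures reproduce. They concern the primary endpoint and are not in dispute. The 457 is used below only as the number randomised per arm.

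**2. Which endpoints lose which patients under the written rules.**

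| Endpoint | Death before the visit | AE withdrawal, no score at the visit |
|---|---|---|
| mRS ≤1, Day 90 (primary) | failure | failure |
| mRS ≤2, Day 90 | kept (scored 5) | missing |
| Ordinal mRS, Day 90 | kept (scored 5) | missing |
| NIHSS 0–1, Days 14, 30, 90 | missing | missing |
| NIHSS change, Day 14 | missing | missing |

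A patient is lost only at visits after death, so the NIHSS effect is smallest at Day 14 and largest at Day 90.

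**3. Size for NIHSS 0–1 (illustration).** The documents give no mortality and no expected NIHSS 0–1 rate. Assume that p = 40% of all randomised patients reach 0–1 in both arms, so the true difference is zero. If a proportion m of an arm has died and all survivors are assessed, the rate among survivors is p/(1 − m).

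| Mortality | Survivors of 457 | Rate in survivors (%) | False difference (points) |
|---|---|---|---|
| 1% v 1% | 452 v 452 | 40.40 v 40.40 | 0 |
| 2% v 1% | 448 v 452 | 40.82 v 40.40 | 0.41 |
| 4% v 2% | 439 v 448 | 41.67 v 40.82 | 0.85 |
| 6% v 3% | 430 v 443 | 42.55 v 41.24 | 1.32 |
| 10% v 5% | 411 v 434 | 44.44 v 42.11 | 2.34 |

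Differences are taken before rounding. The error always favours the arm with more deaths. With p = 50% the 2% v 1% and 10% v 5% rows become 0.52 and 2.92. Counting death as not achieved, on all 457 per arm, restores zero in every row.

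**4. Day-14 NIHSS change (illustration).** Suppose death were given 42, the sum of the item maxima in Appendix 3 with both sides counted. Suppose survivors change by −2.97, the Day-14 figure for the edaravone dexborneol injection group in Protocol 1.3. Each extra 1% of deaths in one arm shifts the mean difference by (42 − baseline + 2.97) × 0.01:

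- baseline 6: 38.97 × 0.01 = 0.39
- baseline 20: 24.97 × 0.01 = 0.25

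The difference of 0.41 reported at Day 14 in that injection trial would be matched by 457 × 0.41/38.97 = 4.8 to 457 × 0.41/24.97 = 7.5 extra deaths, or about 5 to 8. The result depends heavily on the score chosen, which is a reason to prefer ranks.

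**The case against.** The SAP nowhere says that deaths are excluded. The FAS is all randomised patients, and SAP 4.3.2 gives no denominator for the percentages with NIHSS 0–1. That stands for the descriptive tables. It does not rescue the regressions, which cannot use a patient without an outcome. If death is meant to count as failure here, the SAP must say so, as the plan does for the primary endpoint.

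The consequence is also limited. The conclusion rests on the primary endpoint, SAP 4.1.1 calls the efficacy p values nominal, and SAEs, which include deaths, are compared by arm, so an imbalance would be visible. All of that stands. It makes this a fault in secondary endpoints only.

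Four stronger readings are tempting, and the documents do not support them.

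- *Protocol and SAP contradict each other.* A reader might take "Similar approaches were used for binary secondary outcomes" to import the primary's missing-data rules. The same sentence in Protocol 8.4 covers adverse events, to which mRS failure rules cannot apply. It is more naturally about tests, intervals and models. Protocol 8.4, like SAP 4.1.2, ties imputation to the primary outcome.
- *Every secondary endpoint conditions on survival.* Deaths keep an mRS value, so mRS ≤2 and ordinal mRS retain them.
- *About 388 rather than 457 per arm would be analysed for mRS ≤2.* The 15% is a planning allowance ("Considering a 15% dropout rate, 457 subjects are planned to be randomized in each group"), not a forecast of missing Day-90 scores. Withdrawals and emergency unblindings count as dropouts whether or not a score exists, and remote mRS is valid. The minutes of the third IDMC meeting also report follow-up finished in all 914. So 388 is near an upper bound on the loss.
- *Most of an apparent NIHSS gain would be artefact.* Assume 45% v 43% in survivors and mortality of 6% v 3%. The difference is 2.0 points in survivors and 0.45×0.94 − 0.43×0.97 = 0.6 points in all randomised, a fall of about 70%. That share comes from the small assumed effect. With 50% v 40% and the same mortality, it is 10.0 against 0.50×0.94 − 0.40×0.97 = 8.2 points, about 18%. At 2% v 1% it is 10.0 against 9.4, about 6%.

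**Conclusion.** The gap is real and narrow. As written, SAP 4.3.2 removes deaths from the NIHSS regressions at later visits. It also removes from mRS ≤2 the AE withdrawals that lack a Day-90 score, although these count as failures for mRS ≤1. Bias in NIHSS needs deaths that differ between arms in number or in type. The illustration in step 3 varies only the number and assumes that all survivors are assessed. Its range, from zero to about 2.3 points, rests on assumed mortality of up to 10% v 5% and a 40% response rate. Exclusion of patients over 80, with NIHSS above 20, with NIHSS item 1a above 1, or with severe systemic disease and expected survival under 90 days argues against the upper end. The size of the mRS ≤2 inconsistency cannot be estimated from the documents. The change should be made, but neither point touches the primary analysis.

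**What to change.** In SAP 4.3.2:

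- For each binary secondary endpoint (mRS ≤2 at Day 90; NIHSS 0–1 at Days 14, 30 and 90), apply the primary endpoint's rules with all randomised patients as denominator. Death, AE withdrawal or no post-treatment score means not achieved. For other withdrawals, use the score closest to withdrawal.
- For Day-14 NIHSS change, add an analysis that ranks deaths worst, alongside the observed-case regression. Ranking avoids having to choose a score for death.
- Report deaths and missing scores by arm and visit.
- Keep the complete-case results as supportive.

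While editing, reconcile the mRS value for death (5 in Appendix 2) with the 6 that Protocol 8.4 assigns to composite-strategy events.

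The third IDMC minutes record agreement to lock the database. If the data are already unblinded, report these analyses labelled as added later. The cost is SAP wording and some programming, and reported response rates will fall slightly.

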### 2.3 Study Endpoints

- **Primary Efficacy Endpoint**
  - The proportion of patients with mRS score  $\leq 1$  on Day 90 after randomization.
- **Secondary Efficacy Endpoints**

- mRS score on Day 90 of treatment;
  - the proportion of patients achieving a good functional outcome (mRS  $\leq 2$ ) on day 90;
  - the change in NIHSS score from baseline to 14 days.
  - the proportion of patients achieving an NIHSS score  $\leq 1$  on day 14, 30 and 90 days after randomization.
- **Safety Endpoints**

Safety evaluation include:

- adverse events within day 90.
- treatment related adverse events within day 90.
- changes in vital signs and laboratory data before and after treatment.

According to the protocol, exploratory biomarker studies will also be conducted in parallel in this study, and data collection and analysis will be handled separately and not included in this statistical analysis plan.

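### No baseline covariate is specified for the Day-14 NIHSS change, so as written the comparison is an unadjusted change score that usually gives away precision

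*Combined protocol and SAP*

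**What the plan says.** SAP 2.3 lists "the change in NIHSS score from baseline to 14 days" as a secondary efficacy endpoint. Protocol 8.4 describes the analysis: "For changes in NIHSS score from baseline to day 14, means with 95% CIs were calculated for each group". Then, in the same words as SAP 4.3.2, "the mean differences with 95% CI between the groups were estimated by generalized linear regression". The Statistical analysis part of the protocol abstract repeats this. No covariate is named in any of the three places.

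SAP 4.1.3 defines change as a simple difference, "test value at post-treatment follow-up – baseline test value", and defines the baseline value: "The last non-missing data before the first dose is baseline". Secondary endpoints are analysed without imputation (SAP 4.1.2 and 4.3.2).

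Baseline NIHSS is available for every patient because Protocol 4.1 requires a score of 6 to 20 for entry. Randomisation is stratified by onset time and site only (Protocol 5.3, SAP 2.6). Elsewhere in the SAP, baseline NIHSS is only a descriptive variable (4.2.3) and a subgroup factor for the primary endpoint (4.3.1). Where the SAP does adjust, in Sensitivity Analysis 5 of the primary endpoint, it lists its covariates. ANCOVA is in the SAP abbreviation list but is not used in the text.

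**The concern.** This is the only efficacy endpoint that is a continuous change from a baseline on the same scale. Comparing raw changes amounts to fixing the slope of Day-14 NIHSS on baseline NIHSS at exactly 1. If the true slope is different, the change score still correlates with baseline. Two things follow. Variance that baseline could explain stays in the standard error. And if one arm happens to start more severe, part of that difference passes into the estimate: with a slope below 1, the more severe arm appears to improve more. The entry range is wide and severity is not balanced by design, so such an imbalance can arise by chance. What is at stake is the width of the interval and the power for one supportive estimate.

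**Working it through.** **The plan's own figure.** The sample size is for the primary endpoint (50% v 40%, two-sided α 0.05, power 80%, 1:1; SAP 2.5). With pooled variance, n = [1.96·√(2·0.45·0.55) + 0.842·√(0.25 + 0.24)]² / 0.10² = 387.3, so 388 per arm. Then 388/0.85 = 456.5, so 457 per arm and 914 in total. This reproduces. The documents give no SD, power or sample size for the NIHSS change.

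**General result.** Let r = SD(Day 14)/SD(baseline) and ρ = their correlation, so the slope is ρr. In units of the baseline variance:

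- change score: 1 + r² − 2ρr
- baseline-adjusted: r²(1 − ρ²)
- difference between the two: (1 − ρr)², which is never negative and is zero only when the slope is 1.

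The variance ratio, adjusted over unadjusted, is therefore at most 1 in large samples. With r = 1 it is (1 + ρ)/2. Over r from 0.8 to 1.5 and ρ from 0.3 to 0.9 it runs from 0.50 to 0.998. For example, r = 1.2 and ρ = 0.8 (slope 0.96) gives 0.997, which is practically no gain.

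**Illustrative SD.** Protocol 1.3 reports an earlier trial of the injectable product.

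- mRS ≤ 1: 65.61% v 57.48%, 95% CI of the difference 2.63% to 13.63%. SE = 5.50/1.96 = 2.806 points. With equal arms, n = (0.6561·0.3439 + 0.5748·0.4252)/0.02806² ≈ 597 per arm.
- Day-14 NIHSS: −0.41 (−0.73 to −0.09). SE = 0.32/1.96 = 0.163. SD of change = 0.163·√(597/2) ≈ 2.82, treating that interval as unadjusted.

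**Power for 0.41 points, r = 1.** Secondary data are not imputed and the plan allows 15% dropout, so 388 evaluable per arm is the base. The unadjusted SE is 2.82·√(2/388) = 0.2025, so z = 2.02 and power = Φ(2.02 − 1.96) ≈ 53%. For the adjusted analysis, the SE is multiplied by √((1 + ρ)/2).

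| | Variance ratio | 95% CI half-width | Power |
|---|---|---|---|
| Unadjusted | 1 | 0.397 | 53% |
| ρ = 0.3 | 0.65 | 0.320 | 71% |
| ρ = 0.5 | 0.75 | 0.344 | 65% |
| ρ = 0.7 | 0.85 | 0.366 | 59% |
| ρ = 0.9 | 0.95 | 0.387 | 55% |

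The dropout allowance is for Day 90, so losses by Day 14 may be smaller. At the full 457 per arm, power is 59% unadjusted and 72%, 66% and 62% adjusted at ρ = 0.5, 0.7 and 0.9.

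**Chance imbalance.** Assume a baseline SD of 3 to 4 points, which the documents do not give. At 388 per arm, the 95% limits of the baseline mean difference are ±1.96·SD·√(2/388), or ±0.42 to ±0.56 points. With r = 1, an imbalance at those limits shifts the change-score difference by 0.42·(1 − 0.8) ≈ 0.08 points up to 0.56·(1 − 0.5) ≈ 0.28 points, for ρ from 0.8 to 0.5.

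**The case against.** The lack of adjustment is read from silence. No passage says the model is unadjusted, a generalized linear regression can carry covariates, and the ANCOVA abbreviation may be a trace of an intended adjusted model. This stands as a limit on wording: what the documents show is that no baseline covariate is specified. It does not remove the point. The SAP lists covariates where it uses them, and if adjustment was intended the text still leaves the model to the analyst.

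A reader might infer that the estimate is biased. It is not. Over randomisations the unadjusted difference is unbiased, and a change score already subtracts each patient's baseline. What remains is a shift, conditional on the observed imbalance, of (slope − 1) times that imbalance.

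A reader might also infer a definite and large loss of power. The documents give neither ρ nor r, and the 18-point gain needs ρ = 0.3 with equal SDs. The illustration comes from an injectable product against active edaravone, its entry NIHSS range is not stated, and its interval is only assumed to be unadjusted. Its SD and effect may not carry over to a sublingual tablet against placebo.

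Finally, this is one secondary endpoint with nominal p values (SAP 4.1.1). That is correct, and it limits the importance of the point. It is no reason to prefer the less precise model.

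**Conclusion.** The point holds as a free improvement to a secondary analysis. SAP 4.3.2, Protocol 8.4 and the abstract specify no baseline covariate for the Day-14 NIHSS change, and as written the comparison is an unadjusted change score. In large samples with 1:1 allocation, a baseline-adjusted model estimates the same mean difference and is at least as precise. With equal SDs, an assumed correlation of 0.3 to 0.9 gives a variance ratio of 0.65 to 0.95. On the illustrative SD of about 2.8, that is 18 down to 2 points of power at 388 per arm. The gain falls to about zero when the slope is near 1. These figures rest on assumed correlations and SD ratios and on the transferability of the earlier trial. Nothing here supports a claim about the primary mRS result or the planned sample size, and neither changes.

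**What to change.** In SAP 4.3.2, Protocol 8.4 and the abstract, specify a linear model of the Day-14 NIHSS change on treatment, with baseline NIHSS as a continuous covariate and the randomised onset stratum (≤24 h, >24 h) as a factor. Report the adjusted mean difference with its 95% CI as the endpoint's estimate and keep the raw group means as description. State how site, the other stratification factor, is handled.

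Use as covariate the same baseline score that forms the change under SAP 4.1.3. Reconcile this with Protocol 6.1, under which, for thrombolysed patients scored before thrombolysis, "the pre-thrombolysis score should be used as the basis for enrollment". If a second score is recorded between thrombolysis and first dose, the enrolment score and the SAP baseline differ, and the text should say which one enters the change and the model.

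The cost is SAP and protocol wording and one model statement, using data already collected. The model should be fixed before unblinding. If unblinding has already taken place, the adjusted estimate should be labelled as an addition to the planned analysis.
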